### 7.1.8 Access to data

Clinical teams will be able to access their own data. All patients who have been entered within the SCOTS system will be viewed by the clinical teams who entered data. Data which is routinely collected for the National Bariatric Surgery Registry (NBSR) can be entered within the system for surgeons who wish to contribute to this process. Surgeons fully anonymised data (no patient identifiable information) can be exported to a file which surgeons can share with the NBSR if they surgeons wish to contribute. The management and approvals for this will be responsibility of the investigating surgeon and data will not be shared by the SCOTS team.

## Surgical Obesity Treatment Study

2017\_11\_22 SCOTS Protocol v1.6

Page 49 of 61

Glasgow Clinical Trials Unit

## **8 SCOTS STUDY MANAGEMENT**

### **8.1 Study Sponsor**

NHS Greater Glasgow and Clyde Research and Development Office as study sponsors are responsible for the management and conduct (according to GCP). The SCOTS steering committee (SSC) oversee the management and conduct of the study and report to and advise the sponsor on the study. All minutes from both the SCOTS management group (SMG) and SCOTS steering committee (SSC) are copied to NHS Greater Glasgow and Clyde Research and Development Office

### **8.2 SCOTS Study Team**

A study team comprising of the chief investigator, a research lead and a project manager, in collaboration with the data management team based at the Robertson Centre will run the project on a day to day basis. Issues arising from patients or investigators will be managed by this team and those that cannot be resolved by that team will be discussed with the chief Investigator and escalated to the study management group for discussion.

### **8.3 SCOTS Principal investigators**

Each site will have an identified principal investigator who will oversee the application of this protocol locally. Each member of the clinical team involved in the study will be required to register for a login and password to access the e-CRF through the SCOTS data collection portal. Any member of the local clinical teams who has registered username and password and entered data to the SCOTS data collection portal will be a member of the SCOTS Investigators Group. The investigators will be required to enter some initial registration data to link themselves with the surgeons they work with. Planned publications outlined in Table 15-1 will be written on behalf of the SCOTS Investigators Group.

### **8.4 Routine management of study: SCOTS Management Group (SMG)**

The trial will be coordinated from the University of Glasgow by the SCOTS management group (SMG). The SMG will consist of the principal investigator, other co-applicants, project manager and representatives from the Clinical Trials Unit. The role of the group is to monitor all aspects of the conduct and progress of the trial, ensure that the protocol is adhered to and take appropriate action to safeguard participants and the quality of the trial itself. It will be responsible for the day to day running of the trial and budget. It will meet at least 6 monthly, with more meetings initially and as required, and provide information to the steering committee as to the progress of the study.

#### **Surgical Obesity Treatment Study**

Glasgow Clinical Trials Unit

## 8.5 SCOTS Steering Committee (SSC)

SCOTS Steering Committee (SSC) will be established to provide overall supervision of the study and ensure adherence to GCP. It will have an independent chair, a patient representative, and at least two other independent academics along with the principal investigator. Observers from the HTA programme will be invited to SSC meetings, and all SSC papers will be supplied to the HTA programme. The SSC will meet at the start of the study, and annually thereafter.

The role of the SSC is to provide overall supervision of the trial and ensure that it is being conducted in accordance with the principles of GCP and the relevant regulations. The SSC will:

- agree the trial protocol and any protocol amendments
- provide advice to the investigators on all aspects of the trial
- include members who are independent of the investigators, in particular an independent chairperson.

Decisions about continuation or termination of the trial or substantial amendments to the protocol are usually the responsibility of the SSC who advise the sponsor.

**Surgical Obesity Treatment Study**

2017\_11\_22 SCOTS Protocol v1.6

Page 51 of 61

Glasgow Clinical Trials Unit

## 9 STUDY MONITORING/AUDITING

This study is a cohort study. It will therefore be audited on random sampling basis by GG&C auditors on behalf of the GG&C sponsor who audit 10% of sponsored studies per annum.

## 10 PROTOCOL AMENDMENTS

Any change in the study protocol will require an amendment. Any proposed protocol amendments will be initiated by the CI following discussion with the SSC and any required amendment forms will be submitted to the regulatory authority, ethics committee and sponsor. The CI and the SSC will liaise with study sponsor to determine whether an amendment is non-substantial or substantial. All amended versions of the protocol will be signed by the CI and sponsor representative. Before the amended protocol can be implemented favourable opinion/approval must be sought from the original reviewing Research and Ethics Committee (REC) and Research and Development (R&D) office(s).

## 11 ETHICAL CONSIDERATIONS

### 11.1 Ethical conduct of the study

The study will be carried out in accordance with the World Medical Association Declaration of Helsinki (1964) and its revisions (Tokyo [1975], Venice [1983], Hong Kong [1989], South Africa [1996] and Edinburgh [2000]).

Favourable ethical opinion will be sought from an appropriate REC before patients are entered into this study. Patients will only be allowed to enter the study once they have provided written informed consent.

The CI will be responsible for updating the REC of any new information related to the study.

### 11.2 Informed consent

Patients will be informed of the SCOTS study as they discuss weight loss surgery with their clinical teams. They will be provided with an information sheet on the study by a trained member of the clinical teams during a routine clinic visit or during a group session depending on the local patient pathway. The patient will be given time to consider their participation in the study, review the SCOTS information sheet and ask about any concerns they may have. Patients will then be asked to sign the SCOTS consent form.

### Surgical Obesity Treatment Study

2017\_11\_22 SCOTS Protocol v1.6

Page 52 of 61

Glasgow Clinical Trials Unit

## 12 INSURANCE AND INDEMNITY

SCOTS is sponsored by NHS Greater Glasgow & Clyde and NHS indemnity is provided under the Clinical Negligence and Other Risks Indemnity Scheme (CNORIS). In addition, as the protocol authors are employees of the University of Glasgow negligent harm caused by the design of the trial will be covered by the Clinical Trials Insurance policy held by the University of Glasgow.

Investigators working in private healthcare will recruit to this NHS funded study as part of their NHS role and will therefore be covered as detailed above.

## 13 FUNDING

*Funding source:* National Institute for Health Research (NIHR) Health Technology Assessment Programme

*Grant Award number:* 10/42/02

*Original Cost:* £2,124,030

*Amended Cost:* £1,516,255.60

*URL of this project on the NIHR Website:* <http://www.hta.ac.uk/project/2608.asp>

*Start Date:* January 2012

*End date:* June 2021.

*Estimated date of publication in HTA journal series:* Late 2021. This date takes account of time for report preparation and printing based on current average times for these activities.

*International Standard Randomised Controlled Trial Number:* ISRCTN 47072588

*URL of this project on the Controlled Trials Website:* <http://www.controlled-trials.com/ISRCTN47072588>

## 14 ANNUAL REPORTS

A bi-annual progress report will be submitted to NIHR (the funder), the first being submitted 6 months from the date that all funding started (January 2012).

Annual reports will be submitted to the ethics committee and sponsor with the first submitted one year after the date that all study related approvals are in place. These reports will follow the template on the IRAS web site.

### **Surgical Obesity Treatment Study**

2017\_11\_22 SCOTS Protocol v1.6

Page 53 of 61

Glasgow Clinical Trials Unit

## 15 DISSEMINATION OF FINDINGS

Study results whether, negative or positive, will be disseminated. Details of the plan for dissemination are detailed below. Some of the outcomes described may be reported in a number of peer reviewed journal articles. The SCOTS Publication and Presentation SOP (18) describes how this will be managed throughout the study and will ensure that NIHR guidance for publications is adhered to.

**TABLE 15-1: SCOTS PUBLICATION PLANS**

|   | Date     | Description of publication                                                                                                                                                                  |
|---|----------|---------------------------------------------------------------------------------------------------------------------------------------------------------------------------------------------|
| 1 | Jan 2015 | Methods paper: Outlining the methods used in the study including the IT based nutritional blood monitoring and the dataset being collected. Published – Logue et al BMJ Open 2015;5:e008106 |
| 2 | Jul 2017 | Health and socio-economic burden of severe obesity in a population undergoing bariatric surgery.                                                                                            |
| 3 | Jul 2019 | The effect of the pre and post-surgery pathway and surgical experience on weight and complications outcomes after bariatric surgery.                                                        |
| 4 | Jun 2021 | Change in health and socioeconomic factors 3 years after bariatric surgery.

Full HTA report within the NIHR HTA Journal Series.                                                      |

**Surgical Obesity Treatment Study**

2017\_11\_22 SCOTS Protocol v1.6

Page 54 of 61

Glasgow Clinical Trials Unit

### Surgical Obesity Treatment Study

2017\_11\_22 SCOTS Protocol v1.6

Page 55 of 61

## Surgical Obesity Treatment Study

2017\_11\_22 SCOTS Protocol v1.6

Page 56 of 61

## Surgical Obesity Treatment Study

2017\_11\_22 SCOTS Protocol v1.6

Page 58 of 61

Glasgow Clinical Trials Unit

17 Appendix E: Summary of Patient Reported Outcome Questions

Table 17-1 shows a summary table of each set of questions which will be asked of the patient, when they will be asked and if they are validated or not validated.

Questions are classed as not validated in the form they are being asked if they have not been used in a published study and are identified by either a 0 or P in the validated column. 0 means that the set of questions are not validated P means that the questions are partially validated. Partially validated question sets are where a previously published question set has had additional questions added in order to fulfil the SCOTS objectives.

TABLE 17-1: SUMMARY OF SCOTS PATIENT REPORTED OUTCOME MEASURES.

## Glasgow Clinical Trials Unit

| PROMS                                                                 | Total |      | Total |    | Validated | baseline | 2 year | 3 year | Total |
|-----------------------------------------------------------------------|-------|------|-------|----|-----------|----------|--------|--------|-------|
|                                                                       | Total | Male | Femal |    |           |          |        |        |       |
| About you                                                             |       |      |       |    |           |          |        |        |       |
| Demographics – Essential                                              | 1     | 1    | 1     | P  | 1         | 1        | 1      | 1      | 3     |
| Marital Status                                                        | 1     | 1    | 1     | 1  | 1         | 1        | 1      | 1      | 3     |
| Ethnicity                                                             | 1     | 1    | 1     | 1  | 1         | 0        | 0      | 0      | 1     |
| Education                                                             | 1     | 1    | 1     | 1  | 1         | 0        | 0      | 0      | 1     |
| Occupation                                                            | 1     | 1    | 1     | P  | 1         | 1        | 1      | 1      | 3     |
| Health History                                                        |       |      |       |    |           |          |        |        |       |
| Your Medical History                                                  | 1     | 1    | 1     | 1  | 1         | 0        | 0      | 0      | 1     |
| Your Weight History                                                   | 1     | 1    | 1     | 1  | 1         | 0        | 0      | 0      | 1     |
| Family History                                                        | 1     | 1    | 1     | P  | 1         | 0        | 0      | 0      | 1     |
| Family History of Obesity                                             | 1     | 1    | 1     | 0  | 1         | 0        | 0      | 0      | 1     |
| Quality of Life                                                       |       |      |       |    |           |          |        |        |       |
| SF-12 v2 –licence required                                            | 1     | 1    | 1     | 1  | 1         | 1        | 1      | 1      | 3     |
| EQ5D 5L                                                               | 1     | 1    | 1     | 1  | 1         | 1        | 1      | 1      | 3     |
| Patient Health Questionnaire (PHQ-9) (No permissions Free)            | 1     | 1    | 1     | 1  | 1         | 1        | 1      | 1      | 3     |
| Generalized Anxiety Disorder GAD-7 (No permissions Free)              | 1     | 1    | 1     | 1  | 1         | 1        | 1      | 1      | 3     |
| Impact of Weight                                                      |       |      |       |    |           |          |        |        |       |
| Impact of Weight on Quality of Life (IWQOL-Lite) – Licence required   | 1     | 1    | 1     | 1  | 1         | 1        | 1      | 1      | 3     |
| Reproductive Health – Females only                                    | 1     | 0    | 1     | 1  | 1         | 1        | 1      | 1      | 3     |
| Massachusetts Male Aging Study: Single Question Assessment Males only | 1     | 1    | 0     | 1  | 1         | 1        | 1      | 1      | 3     |
| International Prostate Symptom Score (IPSS) Males only                | 1     | 1    | 0     | 1  | 1         | 1        | 1      | 1      | 3     |
| Continence                                                            | 1     | 1    | 1     | 1  | 1         | 1        | 1      | 1      | 3     |
| Reflux Questionnaire                                                  | 1     | 1    | 1     | 1  | 1         | 1        | 1      | 1      | 3     |
| Lifestyle                                                             |       |      |       |    |           |          |        |        |       |
| Smoking                                                               | 1     | 1    | 1     | 1  | 1         | 1        | 1      | 1      | 3     |
| The Alcohol Use Disorders Identification Test: Self-Report Version    | 1     | 1    | 1     | 1  | 1         | 1        | 1      | 1      | 3     |
| Physical Activity IPAC short form self administered                   | 1     | 1    | 1     | 1  | 1         | 1        | 1      | 1      | 3     |
| Nutrition                                                             | 1     | 1    | 1     | 1  | 1         | 1        | 1      | 1      | 3     |
| Personal Outlook                                                      |       |      |       |    |           |          |        |        |       |
| Life Orientation Test (REVISED)                                       | 1     | 1    | 1     | 1  | 1         | 1        | 0      | 0      | 2     |
| Expectations of Surgery                                               | 1     | 1    | 1     | P  | 1         | 0        | 0      | 0      | 1     |
| Surgical Recovery                                                     |       |      |       |    |           |          |        |        |       |
| Post operative pain (1 month acute, 6 month-1 year chronic)           | 1     | 1    | 1     | 0  | 0         | 0        | 0      | 0      | 0     |
| Surgical site infection                                               | 1     | 1    | 1     | 1  | 0         | 0        | 0      | 0      | 0     |
| Skin Excess                                                           | 1     | 1    | 1     | 0  | 0         | 0        | 0      | 0      | 0     |
| Plastic surgery                                                       | 1     | 1    | 1     | P  | 0         | 0        | 0      | 0      | 0     |
| Healthcare and Support                                                |       |      |       |    |           |          |        |        |       |
| Outpatient care                                                       | 1     | 1    | 1     | 1  | 1         | 1        | 1      | 1      | 3     |
| Contacts with other health and social care professionals              | 1     | 1    | 1     | 1  | 1         | 1        | 1      | 1      | 3     |
| Devices and specialist equipment                                      | 1     | 1    | 1     | 1  | 1         | 1        | 1      | 1      | 3     |
| Benefits                                                              | 1     | 1    | 1     | 1  | 1         | 1        | 1      | 1      | 3     |
| Multivitamins and Supplements use                                     | 1     | 1    | 1     | 1  | 1         | 1        | 1      | 1      | 3     |
|                                                                       | 34    | 33   | 32    | 26 | 30        | 23       | 22     | 22     | 75    |

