## Glasgow Clinical Trials Unit

|            |     |                                                                                                                                                                                                                                                                                                                                                                                                                                                                  |
|------------|-----|------------------------------------------------------------------------------------------------------------------------------------------------------------------------------------------------------------------------------------------------------------------------------------------------------------------------------------------------------------------------------------------------------------------------------------------------------------------|
|            |     | consented by a research team member (usually a research nurse).                                                                                                                                                                                                                                                                                                                                                                                                  |
| 03/06/2015 | 1.4 | Amendment 4: Introduction of follow-up letter for patients recruited over the telephone by research nurses at the clinical research facility if completed consent form is not received within two weeks.                                                                                                                                                                                                                                                         |
| 07/02/2017 | 1.5 | Amendment 5; Revised study plan (including timetable & outputs). Patient recruitment stopping at a lower number and earlier than originally planned due to unforeseen recruitment issues. Amendment to clinical objectives and outcomes to reflect smaller sample size and shorter follow-up period. Reduction of post-operative questionnaire frequency to 2 and 3 years post-operatively only. Introduction of modest voucher incentives for PROMS completion. |

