## 1 INTRODUCTION

### 1.1 Background

SCOTS is a prospective cohort study commissioned by the Department of Health (DoH) National Institute of Health Research (NIHR) which will follow bariatric surgery patients for 3 years after their surgery. The NIHR commissioning brief for this study stated: "Obesity is a growing problem in the United Kingdom, with a growing number of people among the morbidly obese. Concomitantly, there is an increase in requests for bariatric surgery but insufficient evidence of long term effectiveness and safety of these procedures. There are existing registries of bariatric surgery, but these suffer from problems of collected data, completeness of follow-up, or data availability for secondary analysis. There is a need for a long term study of bariatric surgery, so that the outcomes and complications of different procedures, their impact on quality of life and nutritional status, and the effect on co-morbidities can be monitored in both the short and the long term." A recent Health Technology Assessment (HTA) (1) concluded that "Bariatric surgery is a more clinically effective intervention for treating obesity compared to non-surgical options" however they qualified this with "Uncertainties remain over the long-term outcomes of bariatric surgical interventions, particularly their impact on weight-related health problems and patient quality of life. Further studies will be required". This study was awarded NIHR HTA funding to address some of the uncertainties around the clinical effectiveness of bariatric surgery in the longer term. The original plan included a 10 year follow up period, however, due to unforeseen recruitment issues (reductions in both NHS & private surgical numbers) the study & statistical plans were reviewed. Following discussions with the NIHR it was agreed that many objectives could still be met from the number of patients currently recruited over a shorter period of follow up (3 years). The protocol has been updated to reflect these changes. Clearly some patients will have completed the 1 month, 6 month and 1 year post-operative questionnaire already. Where appropriate, these data will be used to supplement the year 2 and 3 questionnaires and the health record data in order to deliver the study objectives.

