### 2.2 Secondary Objectives

To establish in a cohort of obese patients who are undergoing bariatric surgery:

1. The physical and mental health and social burden of severe obesity.
2. Incidence of acute and chronic postoperative complications. Acute complications, defined as up to three months post-surgery, will include surgical site infection; chronic complications will include revisional surgery, plastic surgery and chronic pain, for different bariatric surgical procedures.

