| 2.3 | Change in incidence of depression and anxiety compared to baseline levels pre-operatively                                         | eDRIS at National Service Scotland, Patient reported questionnaires                                    | Pre-operatively, ,2,3 years post operatively                           |
| 2.4 | Incidence of complications immediately post-operatively and the need for revisional procedures                                    | Patient reported questionnaires, surgical teams                                                        | Pre-operatively, 2, 3 years post operatively, at time of re-operation. |
| 2.5 | Change in health related quality of life compared to baseline                                                                     | Patient reported questionnaires                                                                        | Pre-operatively, 2,3years post operatively                             |
| 2.6 | Change in glycaemic control, cardiovascular risk factors, chronic kidney disease (CKD), retinopathy, medications in patients with | SCI-DC Scottish National dataset                                                                       | Pre-operatively, 2, 3 years post operatively, at time of re-operation. |

Surgical Obesity Treatment Study

2017\_11\_22 SCOTS Protocol v1.6

Page 27 of 61

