### 3.1.2 Part 2 Patient Reported Outcomes (PROMS) Questionnaire

We will ask patients if they are willing to complete a questionnaire which will include questions on quality of life, overall health and fitness, diet, and anxiety and depression, healthcare utilisation and ability to work. They will also be asked about problems they may have experienced since their surgery such as pain and surgical site infection post discharge.). Where patients are not completing PROMS and there is no reliable clinical weight record, we will write after 3 years requesting completion of a weight questionnaire (simply asking their current weight). The patients will be offered a voucher based incentive of £30 for completing both the year 2 and 3 questionnaires (high street voucher), and £10 for the year 3 weight follow-up questionnaire (for those no longer in clinical follow-up/not completing PROMS)

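### Table 17-1 asks the pain, surgical site infection, skin-excess and plastic-surgery modules at no time point, yet secondary objective 2, Table 3-1 and section 3.1.2 still rely on patient reports; chronic pain has no other named source

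*Protocol*

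**What the plan says.** Amendment 5 (7 February 2017) is described as a "Reduction of post-operative questionnaire frequency to 2 and 3 years post-operatively only", and the synopsis and Table 0-1 now show post-operative questionnaires at 2 and 3 years only.

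In Appendix E, Table 17-1, the Surgical Recovery block keeps four modules: "Post operative pain (1 month acute, 6 month-1 year chronic", "Surgical site infection", skin excess and "Plastic surgery". Each has a zero in every time-point column and a row total of zero. The pain label still carries the dropped timings.

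Other current text relies on patient reports for these topics:

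- Section 2.2, objective 2, limits acute complications to the first three months and includes SSI among them. It adds that "chronic complications will include revisional surgery, plastic surgery and chronic pain, for different bariatric surgical procedures".
- Section 3.1.2 says of the questionnaire: "They will also be asked about problems they may have experienced since their surgery such as pain and surgical site infection post discharge".
- Table 3-1, row 2.4, covers "Incidence of complications immediately post-operatively and the need for revisional procedures". Its sources are patient questionnaires and surgical teams, at baseline, 2 years, 3 years and re-operation.

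Two passages point the other way. Section 1.1 notes that "Clearly some patients will have completed the 1 month, 6 month and 1 year post-operative questionnaire already" and keeps those returns as supplementary data where appropriate. Section 3.1.1 says that record linkage (Part 1), which includes all hospital admissions, fulfils objective 2 among others.

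**The concern.** The four recovery modules belonged to the early post-operative questionnaires. When those were dropped, the modules were given no place in the questionnaires that remained, while the objective, the outcome table and the description of the questionnaire were left as if patients would still be asked. A site or data manager following Table 17-1 collects nothing from patients on these items. An analyst following Table 3-1 or section 3.1.2 expects to find it.

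What is at stake is part of objective 2. Section 1.2.2 gives poor reporting of complications, and of wound complications in particular, as a reason for the study. For components that only the patient can report, no analysis plan can later recover what was never asked.

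**Working it through.** **1. Are the zeros real?** The table header is misaligned, so I rebuilt the totals from the rows.

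- 22 modules are asked at baseline, 2 and 3 years (row total 3).
- 7 modules are asked at baseline only (row total 1): ethnicity, education, medical history, weight history, family history, family history of obesity, expectations of surgery.
- 1 module, the Life Orientation Test, has row total 2.
- 4 Surgical Recovery modules have row total 0.

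Modules: 22 + 7 + 1 + 4 = 34 (printed 34). Baseline: 22 + 7 + 1 = 30 (printed 30). Year 2: 22 + 1 = 23 (printed 23). Year 3: 22 (printed 22). Administrations: 22×3 + 7×1 + 1×2 + 4×0 = 66 + 7 + 2 = 75 (printed 75, and 30 + 23 + 22 = 75).

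The table carries one surplus column, which also sums to 22. The misalignment does not matter here, because the four rows are zero in every time-point column. Had any one of the four been asked even once, the total would be at least 76. So 4 of 34 modules (12%) are asked zero times, and this is in the table rather than a reading fault.

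**2. Who can still hold patient-reported data on these items?** Assume the cut took effect on the amendment date, 7 February 2017. The 1-month questionnaire was then reached only by patients operated on by about 7 January 2017, the 6-month one by about 7 August 2016, and the 1-year one by about 7 February 2016. Recruitment ran to March 2017 (section 2.2) and consent fell between one year and six weeks before surgery (Table 4-1), so operations could continue to about March 2018. Everyone operated on after the cut is never asked. The protocol gives neither the number in each group nor the response rates, so the size of the subset with data cannot be calculated.

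**3. What else covers each component?**

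- *SSI within three months:* linked admissions (section 3.1.1) and complications noted at surgical follow-up (section 4.2.6). In section 4.2.6, however, only appointment date and weight are essential fields, and Tables 0-1 and 4-1 list only weight and re-operation for clinical teams. Infection managed without admission is weakly covered.
- *Revisional surgery:* recorded by surgical teams with its reason (sections 4.2.7 and 7.1.6). Covered.
- *Plastic surgery:* linked when there is an admission. Otherwise no ongoing source is named.
- *Chronic pain:* no ongoing source is named other than the questionnaire.
- *Skin excess:* named in no objective or outcome.

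**4. Does Table 3-1 row 2.4 work as written?** A baseline questionnaire cannot record a post-operative event, and the 2- and 3-year questionnaires do not contain these modules. None of the scheduled times falls inside the three-month acute window. The continuous linkage that does cover it is not listed.

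**The case against.** The strongest reply is that objective 2 was never meant to rest on questionnaires alone. Section 3.1.1 assigns it to record linkage for every participant. Linkage is continuous, so the first three months are not empty. Table 4-1 has the study team contact patients about admissions possibly related to surgery, clinical teams may record any complication at follow-up, and re-operations are captured whenever they occur. The reduction was deliberate and agreed with the funder, and section 1.1 claims only that many objectives, not all, can still be met. Early recovery questions also make little sense at 2 or 3 years.

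Most of this stands, and it limits the point to the components listed in the verdict. It does not remove the conflict: row 2.4 omits linkage, section 3.1.2 promises questions that are not asked, and objective 2 still names chronic pain.

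Three stronger readings are tempting and not supported:

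- A reader might infer that objective 2 has lost all its patient-reported data. Section 1.1 keeps the returns already made; what has stopped is further collection.
- A reader might take the 180 patients with surgery details in section 5.3 (40% of 450, 45% of 400) as the group with early questionnaires as of 29 July 2016. That date belongs to the power calculation and the linkage is undated. The figure also omits later operations before the cut and says nothing about response.
- A reader might infer that reported incidence will be understated, because patients never asked would sit in the denominator. The protocol fixes no such denominator; section 5.1 leaves analyses to separate plans.

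Likewise, the subset with early data is defined by calendar time, so its procedure or surgeon mix may differ, but no figure in the protocol shows that it does.

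**Conclusion.** The inconsistency is real and its consequence is partial. Four of 34 modules are scheduled at no time point, and three current passages contradict this or depend on what it removed. Within objective 2, chronic pain is most exposed. SSI and plastic surgery without admission are weakly covered; acute complications with admission, plastic surgery with admission and revisional surgery have other sources. Skin excess is not needed for any stated objective.

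This should be fixed but does not threaten the study: one secondary objective is affected in part, and the primary outcome, weight change, is not. The conclusion rests on Table 17-1 as printed, whose totals confirm the zeros, and on the sources that the protocol names. It does not depend on the size of the early subset, which is unknown.

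**What to change.** 1. In Table 17-1, schedule the chronic-pain and plastic-surgery items at 2 and 3 years, and reword the pain label, which still refers to dropped time points. The totals become 23 + 2 = 25, 22 + 2 = 24 and 75 + 4 = 79. Skin excess is optional; adding it gives 26, 25 and 81.
2. In Table 3-1 row 2.4, name linked admissions plus surgical-team records as the source for acute complications, with the 0–3 month window stated, so that the row agrees with section 3.1.1.
3. Correct section 3.1.2 to describe what the remaining questionnaires ask.
4. Report patient-reported SSI and acute pain only among patients who were sent the early questionnaires, with that denominator shown.

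The cost is an amendment and a small respondent burden in two questionnaires that, at version 1.6 (November 2017), run until December 2020; linkage is already planned. With recruitment starting around early 2014 (section 2.2), the first patients may already have passed year 3, but they are also the ones who were due the early questionnaires. Patient-reported acute data for those operated on after the cut cannot be recovered, and the report should say so.
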